1.1. Cervical canal stenosis

Stenosis of the cervical canal is the most important complication due to the clinical repercussions that can vary from menstrual cramps followed by hematometrium, infertility and the impossibility of early detection of recurrence and/or recurrence of the premalignant lesion (5, 6).

Studies show a rate of cervical canal stenosis ranging from 3 to 25% after laser conization and 1.3 to 19% when performed with LEEP (5-10). It can be diagnosed within 28 months of conization. (6)

Studies indicate that the variables of wide excision of the entire endocervix (RR 5.07) and extension of the excision of> 2cm (RR 1.95) are associated with a high risk of cervical stenosis after conization. (6)

Although many studies report cervical stenosis after conization, few studies in the literature describe techniques for treating endocervical canal stenosis. When describing some type of intervention, the study is not randomized and with a small number of patients. Among the techniques described there are reports of the use of devices that maintains the patency of the cervical for a brief period in order to avoid restenosis of the canal and maintain the patient's fertility or follow-up in women of non-fertile ages. (11, 12) (13)

Analysis of studies that used some type of device to prevent cervical stenosis

| Authors | Year | N | Device | Length of stay device | Type of study | Post device stenosis rate | Follow-up /  Complications  (N) |
| --- | --- | --- | --- | --- | --- | --- | --- |
| Nasu k et al | 2010 | 4 | DIU-Nylon | 3 months | Case report | 0 | Does not describe/ 0 (zero) |
| Luesley, DM et al | 1990 | 33 | stent | 2 weeks | Pilot Study | 6% | 6 months /  0 (zero) |
| Dorothee Grund et al | 2007 | 1 | Stent Vascular | 9 months | Case report | 0% | 11 months/  0 (zero) |

Table 1

As there is no indication and consensus procedure in the literature to prevent stenosis of the endocervical canal, this study proposes and uses a new device created at the Barretos Cancer Hospital (HCB), called the Uterine Endocervical Canal Dilatation Device (DUDA) (figure 1) in patients undergoing conization in an attempt to assess and avoid the post-CAF stenosis index.

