3. OBJECTIVES

3.1. Primary objective:

To evaluate the effectiveness of a new cervical device called DUDA in preventing late cervical canal stenosis in women undergoing conization with a high-frequency scalpel.

3.2. Secondary objectives:

3.2.1. Assess the safety of using the device;

3.2.2. Compare the quality of life in women with and without the device after surgery;

3.2.3. Compare the rate of visualization of the squamous-columnar junction (JEC) in women who used the device or not (3 and 6 months after surgery);

3.2.4. Describe menstrual periods in women who used device placement after surgery.

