Polyacetal is a plastic material. This material is unique, pure (without additives) with exceptional dimensional stability, low friction coefficient, low moisture absorption and high abrasion resistance. It maintains characteristics when immersed in hot water. High durability, is resistant to biological attacks and impacts, and can even hold weights indefinitely. It also has low weight, high melting point, good impact resistance, high lubricant, thermal insulation, low friction coefficient, high resistance to wear and chemical agents, thus being able to substitute bronze, brass, aluminum with advantages. In addition to the advantages presented, this material is inexpensive. It does not have a porous surface and, therefore, the concentration of substances is inert. As a consequence, it does not generate biofilm, which reduces the risk of infections associated with it. Before use, the device will be sterilized according to the Institution's operational procedure.

Cylindrical at one of its ends, with 4 holes (where the points will be anchored), 2.5 cm in diameter, accompanied by a cylindrical rod with a diameter of 4 mm, central lumen and 2 cm in length (Figures 3, 4 and 5). The nail is introduced into the endocervical canal and the larger cylindrical part is in contact with the external surface of the cervix.

[figure not shown]

Figure 3: Anterior view of the device (DUDA).

[figure not shown]

Figure 4: Rear view of the device (DUDA).

[figure not shown]

Figure 5: Side view of the device (DUDA).

4.6. Description of the conization technique with high-frequency surgery (CAF):

           High-frequency surgery (CAF) is performed by means of a diathermic loop (Figures 1 and 2) connected to an energy source, in order to remove all the so-called transformation zone of the cervix. The size of the resection can be programmed by the surgeon based on the size of the colposcopic lesion and from there choose the best loop size to be used. It is worth remembering that this procedure is part of the conventional treatment of cervical intraepithelial neoplasms and its indication regardless of the acceptance or not of the research participant. Therefore, CAF does not represent the experimental part of the study.

The CAF lasts approximately 20 minutes and follows the technical steps described below:

1) Intravenous sedation;

2) Positioning the patient in the supine position on Allen's leggings and in the lithotomy position;

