3) Asepsis with degerming iodine throughout the perineal and vaginal region. If the patient has an allergy to iodine, asepsis is performed with chlorhexidine gluconate solutions;

4) Placement of sterile surgical drapes;

5) Introduction of the vaginal speculum and identification of the cervix;

6) Passage of acetic acid and Lugol´s iodine in the cervix and vaginal walls to identify positive acetowhite and iodine areas;

7) Local anesthesia with 2% lidocaine with a vasoconstrictor, infusing 2 ml in each quadrant of the cervix (3, 6, 9 and 12h);

8) Passage of the diathermic loop connected to the generating source in “cut” mode (level 60) in a single pass, with or without enlarging the endocervical canal (depending on the indication of each case);

9) Hemostasis with a "ball" electrode connected to the generating source in "coagulation" mode (level 60).

After this surgical procedure, the patient remains in the hospital for a few more hours for recovery from anesthesia and observation of eventual postoperative bleeding. The patient is discharged from the hospital with guidance on the use of analgesics (if necessary) and to abstain from sexual intercourse for at least 30 days due to the risk of bleeding during intercourse.

4.7 Procedure for placing the endocervical device (DUDA):

After the end of the CAF, and with the patient still positioned on the operating table, the surgeon will place the DUDA device on the cervix. Device deployment is quick and requires no more than 5 minutes. It should be noted that this procedure represents the experimental part of the study.

The surgeon will carefully insert the nail into the endocervical canal until the flat circular surface of the device rests on the cervix. By means of the simple suture in four points (2-0 polypropylene thread, atraumatic needle), the device will be fixed to the surface of the cervix. In the event that the residual neck has a very flat surface, the device may be attached to the lateral fornices.

4.8 Criteria for not placing or removing the device:

Even if the participant has signed the Free and Informed Consent Form and the randomization has already been carried out, the DUDA device will not be placed on patients who have any complications during the performance of the CAF and that require additional procedures, such as bed bleeding. surgical procedure requiring hemostatic procedures with suture and/or use of a vaginal tampon.

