4.9.2. Second step: analysis of the effectiveness

The participants in the first stage will not be part of the second. Although the main objective of this step is to evaluate the effectiveness of the device in preventing post-conization cervical canal stenosis, safety and quality of life issues will also be analyzed. The observation period for the second stage will be two years.

In the second stage, 240 participants will be recruited randomly balanced 1: 1 in two groups: one who will receive the DUDA device after CAF and another who will not receive it. Randomization, active search and patient management will take place at the outpatient clinic after the signature of the TLCE by the nurse responsible for clinical research in the department and will be carried out in blocks of 4, through the REDCap program.

4.10. Study outcomes:

4.10.1. Device security:

The safety analysis will be performed up to 30 days after surgery. The definitions of CTCAE (Common Terminology Criteria for Adverse Events) version 4.0 will be adopted as a reference for the security assessment of the device. For that, two main safety events will be considered during its use: vaginal bleeding and uterine infection. Below are the gradations for the two main security events defined by CTCAE version 4.0.

a) Vaginal bleeding:

- Grade 1: mild bleeding, identified on clinical examination or imaging study. No intervention is indicated;
- Grade 2: moderate bleeding; Medical intervention is indicated;
- Grade3: bleeds, intense; need for a blood transfusion; radiological or endoscopic intervention is indicated;
- Grade 4: bleeding determines life-threatening; urgent surgical intervention is indicated;
- Grade 5: death from bleeding.

b) Uterine infection:

- Grade 1: (there is no category for this event);
- Grade 2: moderate symptoms; oral intervention is indicated (eg: antibiotics, antifungal, antiviral);
- Grade 3: intravenous intervention is indicated (eg: antibiotics, antifungal, antiviral); radiological intervention or surgical intervention are indicated;
- Grade 4: infection determines life-threatening; urgent surgical intervention is indicated;
- Grade 5: death from bleeding.

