At the time of the initial visit, preoperative tests (blood count, serum biochemistry, coagulogram, chest X-ray, electrocardiogram and pregnancy test) and pre-anesthetic evaluation of women in whom CAF is indicated will be checked. This preoperative assessment is done on a routine basis and does not include specific aspects of the study. Women who are eligible for CAF and meet the study's eligibility criteria will be invited to participate in the survey. Those who agree will sign the Informed Consent Form at the initial visit.

During this visit, demographic and clinical information will be collected through interviews and consultation of medical records (Annexes 3). At this time, the quality of life questionnaires will also be applied.

4.12.2. Operative and postoperative visits:

On the day of surgery, a form will be filled out with the data pertinent to the surgical procedure. (Annex 4).

Postoperative visits will take place 15 days (1-PO) and 30 days (2-PO) after surgery. (Annexes 5 and 6). The acceptable windows of opportunity for visits will be ± 3 days. During these visits, the participants will undergo a medical consultation, when anamnesis and gynecological physical examination will be carried out. They will also answer the quality of life questionnaires. Any adverse event will be recorded on a specific form each post-operative visit in accordance with the Common Terminology Criteria for Adverse Events v3.0 (CTCAE V3). (Annex 7).

Participants who have the DUDA device will have it removed during the 2-PO visit during the gynecological examination.

4.12.3. Follow-up visits:

Follow-up visits will take place 3, 6, 12 and 18 months after surgery (respectively FUP-1, FUP-2, FUP-3 and FUP-4) according to our flow chart described below. The acceptable windows of opportunity for visits will be ± 10 days. During these visits, participants will undergo a medical consultation, when anamnesis and gynecological physical examination will be performed, which will include the collection of material for cervical cytology, hysterometry to assess the permeability of the endocervical canal and colposcopy to visualize the squamocolumnar junction. The degree of permeability of the channel will be recorded in a specific form. During follow-up visits, quality of life questionnaires will also be applied and adverse events will be recorded and follow-up information will be collected (Annex 8-11).

4.12.4. Surgery information:

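### Randomising in the clinic before the excision lets cone size differ by arm and puts the device-withholding rule after allocation; randomising once the CAF is complete avoids both

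*Protocol*

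**What the plan says.** - **Timing of allocation.** Section 4.9.2: "Randomization, active search and patient management will take place at the outpatient clinic after the signature of the TLCE by the nurse responsible". Section 4.12.1 on consent: "Those who agree will sign the Informed Consent Form at the initial visit". Table 1 (study activities) marks randomisation in the baseline column, ahead of surgery on day 0.
- **Blinding.** Section 4.1 describes an open trial in which the doctor is not blind, because the arm must be known to implant the device. It does not fix when the arm is disclosed.
- **Extent of excision.** Section 4.6: "The size of the resection can be programmed by the surgeon based on the size of the colposcopic lesion". Step 8 of the same section leaves enlargement of the endocervical canal to the individual case. Section 1.1 associates a high risk of stenosis with "wide excision of the entire endocervix (RR 5.07) and extension of the excision of> 2cm (RR 1.95").
- **Placement.** Under 4.7 the device goes in after the CAF has ended, with the woman still on the operating table.
- **Withholding.** Section 4.8 provides that, even where randomisation "has already been carried out, the DUDA device will not be placed on patients who have any complications during the performance of the CAF" and need additional procedures. The control arm has no counterpart to this rule.
- **Block size.** Allocation "will be carried out in blocks of 4, through the REDCap program" (4.9.2), at one hospital (4.2).

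**The concern.** Two events that can affect the outcome or the treatment received fall between allocation and the moment when the arms begin to differ.

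The first is the excision itself. Its extent is partly at the surgeon's discretion, and the protocol treats it as prognostic. A surgeon who knows the arm could cut differently in the two arms, even without intending to. Any resulting difference in stenosis would be attributed to the device or would mask its effect.

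The second is the decision under 4.8 not to place the device. It is taken after randomisation and changes treatment in one arm only. If the women concerned stay in their allocated arm, the contrast shrinks. If they left it, the arms would no longer be comparable.

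A statistical analysis plan can settle how the second group is analysed. It cannot undo an imbalance in cone size that arose at surgery.

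**Working it through.** **1. The plan's own figure.** Section 5.2 gives 15-20% versus 6%, alpha 5%, power 80%, 1:1 allocation, and 104 to 203 per group. The two-sided pooled-variance formula is

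n = [1.96·√(2p̄q̄) + 0.84·√(p₁q₁ + p₂q₂)]² / d²

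It gives 90 (20% versus 6%) and 181 (15% versus 6%). With the continuity correction these become 104 and 203, which match the protocol exactly.

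**2. Power at the planned 120 per arm.** Power = Φ{[d·√120 − 1.96·√(2p̄q̄)] / √(p₁q₁ + p₂q₂)}, without continuity correction; a corrected test would have less.
- 15% versus 6%: [0.0900 × 10.954 − 1.96 × 0.4335] / 0.4288 = 0.318, so 62.5%.
- 20% versus 6%: 90.2%.

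**3. Withheld devices, analysed as randomised.** The documents do not give the share w of device-arm women from whom the device is withheld, so w is assumed. These women are also assumed to have the control rate. The device-arm rate is then (1 − w) × 6% + w × control rate, and the difference shrinks by the factor 1 − w. At w = 10% it falls from 9.0 to 8.1 points, or from 14.0 to 12.6.

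| w (assumed) | Power, 15% control | Power, 20% control |
| --- | --- | --- |
| 0% | 62.5% | 90.2% |
| 5% | 57.2% | 86.2% |
| 10% | 52.0% | 81.4% |
| 15% | 46.8% | 75.9% |
| 20% | 41.8% | 69.8% |

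To hold 80% power at w = 10% with the protocol's own formula, the size per arm rises from 203 to 257 (15% control) or from 104 to 132 (20% control).

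**4. Withheld women dropped from the device arm (hypothetical).** Suppose the device does nothing, a share c = 5-15% of excisions is complicated, and stenosis in those women is k = 1.95 to 5.07 times that in the others. All of this is assumed; the values of k are borrowed from section 1.1, where they describe extent of excision, not complications. The remaining device-arm women have rate control / (1 − c + c·k).
- Smallest case: 15% / (0.95 + 0.05 × 1.95) = 14.3%, a false benefit of 0.7 points.
- Largest case at 15% control: 15% / (0.85 + 0.15 × 5.07) = 9.3%, or 5.7 points.
- At 20% control the range is 0.9 to 7.6 points.
- Over the whole grid, the chance of a significant false benefit is 3.5% to 32.5%, instead of 2.5%.

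**5. Cone size.** Assume wide excision in 30% of control women and in 20% of device women, with no device effect. With RR 5.07 the ratio of stenosis rates is (1 + 0.3 × 4.07) / (1 + 0.2 × 4.07) = 2.221 / 1.814 = 1.22, control over device. At 15% control stenosis this is 2.75 points; at 20% it is 3.7. With RR 1.95 the gaps are 1.1 and 1.5 points. If the device arm had 40% instead, the gaps would be the same size in the other direction. The planned effect is 9 to 14 points.

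**6. Blocks of 4.** The fourth allocation always follows from the first three. The third is known when the first two are alike, which has probability 1/3. The expected share known with certainty is (1 + 1/3) / 4 = 1/3.

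**The case against.** The strongest reply is that nothing in the protocol shows a biased comparison. Four readings go further than the text allows.

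- **That 4.8 removes high-risk women from one arm.** It says only that the device is not placed. Sections 4.9.2 and 6 define and compare the groups as randomised groups, and the analysis set is commonly left to a statistical analysis plan, which is not at hand. Section 1.1 links stenosis to extent of excision, not to intra-operative bleeding, suture or tampon, so a higher risk in these women is an assumption.
- **That the objectives compare by device received.** The wording "in women who used the device or not (3 and 6 months after surgery") belongs to secondary objective 3.2.3, on visualisation of the squamocolumnar junction. The primary objective in 3.1 does not contrast users with non-users.
- **That the surgeon does know the arm and cuts accordingly.** Section 4.1 ties that knowledge to implantation, which follows the CAF, and 4.6 ties resection to clinical findings. Knowledge before the cut is not prevented, but it is not documented either. The 30% versus 20% split is illustrative.
- **That the nurse who recruits also allocates.** The translated sentence is ambiguous: the nurse may be attached to the consent signature only. Predicting one third of allocations also requires someone to track past allocations and block boundaries.

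All four limits stand. They leave the order of events as it is. The protocol's own reason for unblinding does not require the arm to be known before the excision, and 4.8 expressly foresees withholding after randomisation.

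**Conclusion.** The concern holds as a design weakness, not as a demonstrated bias.

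- **Cone size:** it can differ by arm because allocation precedes the excision and is not concealed from the surgeon. An assumed 10-point imbalance moves the result by 1.1 to 3.7 points, in an unknown direction.
- **Withheld devices:** under analysis as randomised they cost power but create no false benefit. The loss is about 10 percentage points at 15% versus 6% and about 9 at 20% versus 6%, if 10% are withheld. It matters because 120 per arm is already below the 203 that the protocol computes for 15% versus 6%. Bias from this source arises only if the women are excluded or analysed by device received, which the protocol does not state.
- **Fixed block of 4:** valid but secondary, with one third as an upper bound.

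Every size other than the 104-203 range rests on an assumed withholding, complication or excision rate. Severity: should fix.

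**What to change.** 1. Keep consent, baseline data and quality-of-life forms in the clinic. Randomise in REDCap in the operating room once the CAF and haemostasis are complete and the existing 4.8 criteria do not exclude the device. Those clinical criteria stay as they are; only the time of allocation moves.
2. State that every randomised woman is analysed in her allocated arm. This is still needed, because the early removals foreseen in 4.8 (invasive carcinoma on histology, perceived risk, or the woman's request) occur after allocation under any scheme.
3. Replace the fixed block of 4 with randomly varying block sizes that are not disclosed to recruiting staff.

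Keeping the allocation from the surgeon until haemostasis is complete would deal with cone size alone, but would leave the withholding after randomisation.

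**Cost.** Sections 4.8 and 4.9.2 and Table 1 are amended and a new REDCap list is loaded. REDCap access and a sterile device are needed at each eligible surgery. A few consented women are never randomised, and the results apply to women with an uncomplicated CAF. The change has to be made before recruitment to the second stage, because an imbalance created at surgery cannot be undone later.

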5. SAMPLE CALCULATION

5.1. First step:

For the safety analysis of the device, 25 women will be included, as advised by the National Ethics and Research Commission (CONEP).

5.2. Second stage:

The sample calculation assumed the premise of a cervical canal stenosis rate of approximately 15% to 20% after the CAF described in the literature and reduced to 6% with the use of an endocervical device according to the uncontrolled trial by Luesley et al (11) Considering this difference in stenosis rates (15-20% vs. 6%), an alpha error of 5%, a beta error of 20% and a balanced allocation 1: 1, the sample estimate ranges from 104 to 203 in each group. Therefore, this stage of the study will recruit 120 women in each arm, totaling 240 participants.

It is estimated that recruitment will take place between 1 to 3 weeks in the first stage and between

25 to 30 weeks in the second stage, since the potential for recruitment is 06 to 10 surgeries per week.

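### Allocation and the stated stenosis test ignore excision extent, the protocol's own strongest cited risk factor, which gives up some precision; separately, the 15-20% control rate sits at and above the top of its cited LEEP range

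*Protocol*

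**What the plan says.** - **Risk factor.** Two predictors of post-conization stenosis are cited in section 1.1 of the protocol: "the variables of wide excision of the entire endocervix (RR 5.07) and extension of the excision of> 2cm (RR 1.95").
- **Variation between women.** Step 8 of the technique in section 4.6 has the loop passed once, "with or without enlarging the endocervical canal (depending on the indication of each case"). The same section says that the surgeon can plan resection size from the colposcopic lesion.
- **Eligibility.** Sections 4.3 and 4.4 require biopsy-proven CIN 2/3, an indication for CAF (LEEP) and age 18 to 65. They exclude pregnancy, earlier conization, women who do not understand or accept the study, and vulnerable groups. No criterion concerns the type or depth of excision.
- **Allocation.** Section 4.9.2: randomisation takes place in the outpatient clinic after consent, is 1:1, and "will be carried out in blocks of 4, through the REDCap program". No stratification factor is named.
- **Analysis.** Section 6 compares stenosis between arms at each time by chi-square or Fisher's exact test, without adjustment.
- **Planning rates.** Section 5.2 starts from a "cervical canal stenosis rate of approximately 15% to 20% after the CAF described in the literature". For the device arm it takes 6%. Section 1.1 gives the published range as "1.3 to 19% when performed with LEEP".

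**The concern.** The protocol cites a fivefold risk factor for its own primary outcome, lets that factor vary with the surgical indication, and then uses it neither in eligibility, nor in allocation, nor in the stated test. Two things follow.

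First, the arms may differ by chance in their share of extensive excisions. An unadjusted test also leaves the variation caused by that factor in the error term. In an open, single-centre trial of 240 women, a visible imbalance on this factor would make the result harder to defend, even though the test remains valid.

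Second, the control rate depends on case mix, and case mix is unrestricted. The assumed 15-20% lies at the top of the range that the protocol quotes for this procedure, and 20% is beyond it. If most excisions are limited ones, there may be too few events to answer the primary objective.

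**Working it through.** **Inputs.** From section 5.2: "an alpha error of 5%, a beta error of 20% and a balanced allocation 1: 1"; control rate 15-20%; device rate 6%; 120 per arm. From section 1.1: RR 5.07 and the LEEP range 1.3-19%. Assumed, because the protocol does not give it: the share q of women with planned endocervical extension, taken as 20-40%. Also assumed: that such extension carries the full RR 5.07. The 17.5% control rate used below is the midpoint of 15% and 20%.

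**1. The protocol's own sample size.** Two-sided 5%, 80% power, pooled normal formula, then the continuity correction n' = (n/4)(1 + sqrt(1 + 4/(n d)))^2, with d the difference in rates:
- 15% v 6%: n = 180.9, n' = 202.6, so 203.
- 20% v 6%: n = 89.4, n' = 103.2, so 104.

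Both ends of the stated 104 to 203 reproduce exactly.

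**2. Stratum rates at q = 0.30, overall control rate 17.5%.**
- Without extension: 0.175 / (0.7 + 0.3 x 5.07) = 0.079.
- With extension: 5.07 x 0.079 = 0.40.

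**3. Chance imbalance under unstratified blocks of 4.** The SD of the between-arm difference in share is sqrt(2 x 0.3 x 0.7 / 120) = 0.059. A 2-SD imbalance, which occurs in roughly 5% of trials counting both directions, has this effect:
- Placed wholly in the control arm: 2 x 0.059 x (0.40 - 0.079) = 3.8 points. This is an upper figure.
- Split evenly between arms, with device relative risk 0.06/0.175 = 0.343: 0.059 x 0.32 x 1.343 = about 2.5 points.

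The assumed effect here is 17.5 - 6 = 11.5 points.

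**4. Power and error rate by simulation** (40,000 trials per setting, 17.5% v 6%, 120 per arm, q = 0.30, RR 5.07):

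| Allocation | Test | Power |
| --- | --- | --- |
| Unstratified | chi-square, as stated | 81% |
| Stratified | chi-square | about 82% |
| Unstratified | Mantel-Haenszel | 84% |
| Stratified | Mantel-Haenszel | 84-85% |

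- At q = 0.2 and 0.4, the last row is about 85% and 84%.
- With RR 2.5 instead of 5.07, the gain from the stated plan to the last row is about 1 point.
- Under no device effect, the stated plan rejects in about 5% of trials. Stratified allocation with an unadjusted test is somewhat conservative (about 3-4%), so stratum and stratified test belong together.

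**5. Power of 120 per arm against a fixed 6%** (normal approximation, no continuity correction; it gives 79% at 17.5%, slightly below the simulated 81%):

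| Control rate | Power |
| --- | --- |
| 20% | 90% |
| 19% | 87% |
| 17.5% | 79% |
| 15% | 62% |
| 12% | 37% |
| 10% | 21% |

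About 17.7% is needed for 80%. If the device instead keeps a relative risk of 0.4 (6/15), power at a 10% control rate is 45%.

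**6. Dependence on case mix.** The overall rate is r(1 + q x 4.07), with r the rate without extensive excision. For an assumed r of 5%, it is 9.1%, 11.1% and 15.2% at q of 20%, 30% and 50%.

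**The case against.** The strongest case against is that this is a refinement of an acceptable design, and much of it stands.

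- **Validity.** A reader might infer that unstratified allocation biases the comparison or inflates false positives. It does neither: randomisation is unbiased, and chance imbalance is already counted in the test's error rate.
- **Source of the gain.** A reader might credit stratified allocation with the extra power. Step 4 shows that it adds about 1 point or less; the adjusted test supplies nearly all of it. Adjustment is often left to an analysis plan, and none is shown here. Against that, Section 6 does state an unadjusted test, and a stratum cannot be added once allocation is complete.
- **The factor.** RR 5.07 concerns wide removal of the whole endocervix. Applying it to any planned enlargement is an inference, and every figure shrinks if the overlap is partial. The protocol reports an association with high risk; it does not say that stenosis is confined to these women.
- **Timing.** Section 4.6 supports planning resection size from colposcopy. It does not show that the decision to extend is settled when the woman is randomised in clinic. The plan may change at surgery.
- **Eligibility.** It would be wrong to say that every woman having LEEP can enter, because histology, age and earlier conization all restrict entry. Only excision extent is unrestricted.
- **Event rate.** Most of 15-20% does lie within 1.3-19%. Rates of 10% or 12% are illustrations inside that range, not predictions.

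**Conclusion.** The point holds as a modest loss of precision plus a separate weakness in the planning premise.

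On precision, the gain available is about 3 to 4 percentage points of power if planned extension is present in 20-40% of women and carries the full RR 5.07, and about 1 point if the relative risk is nearer 2.5. Neither the share nor that equivalence is in the protocol. Balance on the factor also makes a single trial's result easier to defend.

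On the premise, the protocol's own cited range does not support 15-20% as a central expectation for a population unrestricted by excision extent. At 15%, the lower end of its own assumption, 120 per arm gives about 62% power, not 80%.

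A reader might infer that stratifying would protect the trial against a low event rate. It would not: the shortfall comes from case mix and the assumed rate, and it stays whatever the allocation scheme.

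**What to change.** - **Section 4.9.2:** record planned endocervical extension (yes/no) before allocation and use it as the single REDCap stratum, keeping blocks of 4 within it.
- **Section 6:** compare stenosis with a Mantel-Haenszel test stratified by the recorded plan, not by what was done at surgery.
- **Section 5.2:** state that 15-20% lies at and above the upper end of the 1.3-19% LEEP range in section 1.1, and report the power of 120 per arm against 6% at lower rates (about 62% at 15%, 37% at 12%, 21% at 10%). Whether to re-base the sample size on the expected case mix is then an open decision.

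**Cost:** one data field and wording in three sections, with no change to surgical care and no extra patients for the stratum and test. The small downsides are that the plan must be recorded before allocation and may change during surgery, and that the stated power will look less favourable.
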